**Introduction**

Femoroacetabular Impingement syndrome (FAIS) is a well-recognised pathological entity and a common cause of hip and groin pain in young adults [1]. A recent epidemiological study reported a high prevalence of FAIS (47%), within a sample (n=200, aged 16-65 years) representative of the UK population [2].The pathology encompasses a morphological abnormality of the femur (Cam) or the acetabulum (Pincer) and can lead to chondro-labral dysfunction and eventually in some cases early onset of osteoarthritis [3].Additionally, deficits in muscle strength and range of motion (ROM) may lead to altered or increased hip joint loads causing detrimental effects [4, 5]. Non-surgical management such as physiotherapy will assist in modifying hip joint loads and address the above physical impairments, although, evidence of the effectiveness of such interventions are currently lacking [6].

Excision of the FAI lesion and addressing chondro-labral pathology through surgical procedures like hip arthroscopy may be necessary to provide better medium to long term outcomes [7]. Innovations in diagnosis and surgical techniques has resulted in an exponential growth of hip arthroscopy procedures in the past decade [8]. Two recent multicentre randomised controlled trials (RCTs) have found significant improvement in outcomes following hip arthroscopy compared to physiotherapy [9, 10]. However, results demonstrate that only half (51%) of participants showed significant improvement on the primary outcome measure - iHOT33 (mean difference 6·8 points; 95% CI 1·7–12·0) [9]. Several factors have been shown to influence the outcomes after hip arthroscopy. These include, the presence of osteoarthritis, severe dysplasia, inadequate removal of the impingement lesion, and soft tissue injury sustained during the procedure [3, 11, 12]. Amongst the non-surgical factors are prolonged waiting times leading to the chronicity and deconditioning of the muscles [13], deficits in muscle strength [14], psychological distress [15] and presence of concomitant pathologies like gluteal tendinopathy [16] and athletic pubalgia [17]. Therefore, early identification and optimisation prior to surgery will be crucial in delivering optimal post-operative outcomes.

Pre-operative rehabilitation intervention or ‘prehabilitation’ is the process of enhancing a patient’s functional capacity prior to surgery in order to improve post-operative outcomes [18]. Prehabilitation interventions have been tested and found to be beneficial across all age groups and various surgical pathways including orthopaedics [19, 20]. It is important for interventions included in the prehabilitation programme to be specific to the clinical condition, personalised and tailored to patient needs. A person-centred approach, which allows patients to take control of their own outcomes through prehabilitation, places the patient at the core of their peri-operative pathway [21]. This will heighten their motivation to make positive behavioural changes during the pre-operative phase and provide both peri and post-operative benefits [22].

Although the effectiveness of prehabilitation has been investigated in a wide variety of orthopaedic conditions, its effectiveness in patients undergoing hip arthroscopy has received little attention and not been studied in depth. Recently, a small pilot study on FAIS patients (n=18) favoured prehabilitation over standard care [23]. The findings suggested that a definitive trial to evaluate effectiveness would be valuable.

**Aim**

To evaluate the feasibility, suitability, acceptability and safety of a novel prehabilitation programme for FAIS to inform a future definitive randomised control trial to assess effectiveness.

**Objectives**

The objectives of the study and success criteria are detailed in Table 1.

**General Objectives**

To assess the feasibility, suitability, acceptability and safety of prehabilitation intervention including the following:

- Recruitment procedures
- Data collection methods
- Follow-up procedures
- Determine sample size for a full trial to test its effectiveness

**Specific objectives**

**Feasibility**

- To evaluate participant recruitment and attrition rates [24]
- To evaluate follow-up rates and response rates to questionnaires [24]
- To evaluate the ease of using the Physitrack app [25]
- To evaluate the time and effort of clinicians to deliver the intervention [24]
- To evaluate fidelity of intervention delivery [26]

**Suitability**

- To evaluate suitability of the outcome measures [27]
- To evaluate participant adherence with prehabilitation interventions [24]
- To evaluate the time taken to undertake each phases of the study [24]
- To evaluate the appropriateness of incorporating a novel prehabilitation intervention for FAIS into the current NHS services infrastructure [28]

**Acceptability**

- To evaluate the acceptability of interventions to patients and clinicians [27]
- To evaluate the willingness of patients to participate in a full RCT in the future [27]

**Safety**

- To evaluate the safety of the intervention [24]

**Methods**

This feasibility trial protocol is registered with ISRCTN Registry No. [15371248](https://gbr01.safelinks.protection.outlook.com/?url=https%3A%2F%2Furldefense.com%2Fv3%2F__https%3A%2Fgbr01.safelinks.protection.outlook.com%2F%3Furl%3Dhttps*3A*2F*2Fwww.isrctn.com*2FISRCTN15371248%26data%3D05*7C01*7Canuj.punnoose*40nhs.net*7C9fa1d1cb31ac4eea522208db208040f0*7C37c354b285b047f5b22207b48d774ee3*7C0*7C1*7C638139507488348179*7CUnknown*7CTWFpbGZsb3d8eyJWIjoiMC4wLjAwMDAiLCJQIjoiV2luMzIiLCJBTiI6Ik1haWwiLCJXVCI6Mn0*3D*7C3000*7C*7C*7C%26sdata%3DjhuBzsDF9dAXwZp2WybtzoFfhM2QmT*2BD5nBgph95ur8*3D%26reserved%3D0__%3BJSUlJSUlJSUlJSUlJSUlJSUlJSUl!!NLFGqXoFfo8MMQ!o5gyU8Yg-xtoOcV03CIwwOj7buBTB7wtM4htRAAEHbePs9xDAJES7cOV8pIh9cNPci9izQN619tq1p8G25HStGs06plu7McpEOMnDzY%24&data=05%7C01%7Canuj.punnoose%40nhs.net%7C7ea3de2b1fe449cc8fce08db208cf620%7C37c354b285b047f5b22207b48d774ee3%7C0%7C1%7C638139562080717319%7CUnknown%7CTWFpbGZsb3d8eyJWIjoiMC4wLjAwMDAiLCJQIjoiV2luMzIiLCJBTiI6Ik1haWwiLCJXVCI6Mn0%3D%7C3000%7C%7C%7C&sdata=qUiiP46We8crUy1mnwHx6QBKHD8yqnz7a3Iu3yI%2BYI4%3D&reserved=0) and reported as per  CONSORT 2010 statement: extension to randomised pilot and feasibility trials to ensure transparency and reproducibility [30]. All patient and public involvement meetings will be evaluated using an Impact log and reported in line with the GRIPP2 short form reporting checklist [31].

This feasibility trial will use a mixed methodology encompassing the following;

- A quantitative two arm parallel group feasibility trial
- Embedded qualitative component (Physiotherapists & Research participants) using thematic analysis

**Design**

A randomised control study design (RCT) is considered as gold standard when evaluating

the effectiveness of an intervention as it eliminates various biases prevalent in other study designs [32]. However, a RCT can be challenging with several unknown factors at play (recruitment, adherence, attrition, acceptability and suitability of interventions). Therefore, prior to evaluating the effectiveness of an intervention, researchers are encouraged to assess its feasibility, suitability of outcomes and optimise the overall design of the trial to ensure any uncertainties are addressed prior to a full trial [26, 33]. This study design will allow to test the feasibility of a novel prehabilitation intervention in an NHS setting, measure adherence, evaluate fidelity of intervention delivery and assess the suitability and acceptability of the interventions.

**Participant demographic data**

Participant baseline demographic data such as age, gender, height, weight, Body mass index, duration of symptoms and work status will be recorded. Additionally, details of their physical examination, investigations and past medical history recorded as a part of their routine care may be collected and used for the purpose of this study.

**Trial component**

A prospective two group parallel feasibility trial will be conducted to answer the above trial objectives [27].

Outcome measures will be obtained at baseline (prior to prehabilitation intervention), after prehabilitation before surgery, and at 6 weeks+/- 4 weeks and 6 months+/- 4 weeks (planned primary endpoint for definitive RCT) postoperatively when participants attend the research site for clinical care. Additionally, all patient reported outcome measures will be captured at 12 months+/-4 weeks post-op (secondary end point). Physical outcome measures will be taken onsite during the participant’s clinical visits and patient reported outcomes will be collected via the Physitrack app (<https://www.physitrack.com/clinical-studies>) or mailed to the participants at various follow-up points (see Fig. 2).

**Participants**

The study will be conducted at the Young Adult Hip Service in Addenbrooke’s – Cambridge University Hospital NHS Foundation Trust, Cambridge, UK, which has a good track record of recruiting to trials and managing them as well. Potential participants will be identified from the waiting list for hip arthroscopy at the NHS site. This will be performed by the Chief Investigator (CI) or the Principal Investigator (PI) who is a part of the direct clinical care team. Potential participants for the study will be contacted if their surgical date in the future will allow appropriate time for the consent process, randomisation and 8 weeks of prehabilitation intervention.

A Patient Information Sheet (PIS) will be provided in clinic or mailed to participants to facilitate the consenting process. The research team will ensure that they adequately explain the aim, study treatment, potential benefits or harm of taking part in the trial to the participants. They will also re-iterate that participation is voluntary and participants can withdraw from the study at any time, without giving a reason. Participants will be phoned after 1 week from when they have received the PIS to see if they are interested in taking part. For patients interested in participating, the consent process will be completed over the phone. The consent process will be witnessed by a member of staff independent of the trial team. The PI (or delegate) will sign the consent form as the person receiving consent and the independent witness will sign the consent form to confirm that the consent process was followed, and the participant gave their verbal consent to take part. Participants will be asked to sign the consent form when they come for their surgery, and they will receive a copy.

**Inclusion criteria**

All patients referred to Cambridge Young Adult Hip Service (aged 16-50 years), undergoing hip arthroscopy for the management of FAIS.

**Exclusion criteria:**

- Previous hip disease such as Perthe’s, Slipped upper femoral epiphysis or avascular necrosis [9]
- Participants who are unable to give full written consent
- Participants who are not fluent in English
- Pre-existing neuromuscular conditions like Motor Neuron Disease or Multiple Sclerosis
- History of any previous hip surgery
- History of any previous hip arthroscopies

**Randomisation and blinding**

Following baseline evaluation, participants will be randomly allocated to one of the two groups (prehabilitation or usual care) by the PI using a computer-generated random allocation sequence. This will be uploaded to a secure database known as REDCap (Research Electronic Data Capture) and all study personnel will be blinded to the allocation sequence ensuring adequate concealment [67, 68]. REDCap is a secure, web-based software platform designed to support data capture for research studies, providing 1) an intuitive interface for validated data capture; 2) audit trails for tracking data manipulation and export procedures; 3) automated export procedures for seamless data downloads to common statistical packages; and 4) procedures for data integration and interoperability with external sources.

Blinding participants and clinicians delivering interventions will not be possible as both will be aware of the intervention and allocation. However, the content of the programme will only be known to participants in the intervention group thereby reducing the risk of cross contamination between groups [34]. Physical outcome measures will be measured by a blinded assessor who will be trained by the PI to ensure standardisation and improve reliability of the assessment.

**Interventions**

All participants, regardless of group allocation, will receive standard peri & post-operative care. A record of their analgesia consumption will be noted during their follow-up appointments in a logbook by a member of the research team.

**Prehabilitation Intervention**

Interventions are described based on the Template for Intervention Description and Replication (TIDieR) [35]. The exercise intervention used in this study was developed utilising the findings of a systematic review on prehabilitation and an expert panel consensus methodology to define the core components of the intervention. The intervention will be delivered over a period of 8 weeks prior to surgery and will target 5 domains- muscle strength, range of motion, proprioception, cardiovascular fitness and addressing co-existing pathologies. Literature suggests high prevalence and poorer outcomes of depression and anxiety in people with FAIS [15, 36], and the intervention will therefore also include an in-person educational session delivered by the PI to provide greater understanding of the surgery to alleviate anxiety and help manage patient expectations. The intervention will include at least four in-clinic face-to-face sessions (once a fortnight) with an experienced physiotherapist (>2 years’ experience in treating musculoskeletal conditions including FAIS) followed by six to eight remotely monitored sessions (once a week) using a telehealth system. The number of sessions will be determined based on physiotherapist assessment and intensity and complexity of exercises will be gradually increased depending on each participant’s individual progress (Fig 1). Due to the wide variation of patient characteristics within the FAIS population (e.g. sedentary or athletic) interventions will be tailored according to individual participant’s capabilities.

**Use of Physitrack app and Telehealth system:**

Physitrack provides exercise information and videos via website and apps. Dosage and frequency of the exercises can be selected, and patients will be encouraged to record completion of the exercises enabling the physiotherapist to measure adherence via the app. Physitrack has been found to improve adherence and patient confidence and is utilised across several NHS Trusts in the UK [37]. Additionally, the use of Physitrack’s tele-rehabilitation would enable physiotherapists and patients to interact with each other via video providing reassurance of the correct exercise techniques and progression.

The participants in the intervention group will use Physitrack which provides photos and videos of the prescribed exercises and those unable to use the app will be provided with paper-based instructions. Additionally, patients will be asked to complete their exercises at home twice weekly.

**Training of Physiotherapists delivering the prehabilitation intervention**

The prehabilitation intervention will be delivered by experienced physiotherapists as described above. All the rehabilitation components are standard clinical therapies familiar to a trained physiotherapist. The physiotherapists will undergo training (by PI) on how to deliver these components together as per the protocol for this study. A representative from Physitrack will be invited to deliver training on the use of the app.

**Usual care intervention**

As per the host hospital’s current clinical guidelines, the usual care intervention consists of advice to continue with normal activities and no prehabilitation therapy.

**Qualitative component**

An embedded qualitative component will be utilised to answer specific trial objectives and to refine and adapt the design prior to the full RCT. Prior to participating in the qualitative study, participants will be provided with an information leaflet and opportunity will be given to raise any questions to the researchers regarding the processes. Consent from all participants will be obtained prior to commencement. All qualitative data will be recorded and transcribed verbatim. Transcripts will be returned to participants for review and edited prior to analysing the data.

**Physiotherapists**

In-depth face to face semi structured interviews will be used to evaluate the views of the Physiotherapists (n=4) regarding the feasibility, suitability and acceptability of the intervention, outcome measures as well as the Physitrack app in an NHS setting as described below. The interviews will be conducted by the PI within one year of commencement of the study to gather qualitative data. Appropriate questions for the interviews will be developed by the PI and the supervisory team. A patient and public involvement group will review the questions for clarity and appropriateness [38].

**Research participants**

Focus groups with research participants will be conducted following the 6 months assessment point to evaluate the research objectives. A purposive sample of 6-8 patients at different points of their research pathway (pre-op & post-op) will be included as recommended in the literature[39]. A predetermined topic guide developed by the PI and reviewed by the PPI panel will be used for the focus group. The focus group will be conducted by 2 researchers: the PI (facilitator) and a supervisor (observer) and two or more sessions maybe conducted until data saturation has been achieved.

**Outcome measures**

**Feasibility measures**

Feasibility parameters will be utilised to answer the objectives as per Table 1. The recruitment rate will be determined by the number of participants who are eligible and consent to participate in the study. Attrition will be defined by the number of consenting participants who drop out during the study. Timing of dropouts and reasons (where provided) will be explored to determine if the follow-up points are appropriate prior to a definitive RCT. Follow-up rates and response rates to questionnaires will be collected at each follow-up point. The usability of the Physitrack app and tele-rehabilitation will be evaluated using a modified System Usability Scale (SUS)[25]. Time and effort of clinicians delivering the interventions will be captured via the hospital’s electronic system.

Treatment fidelity is the extent to which an intervention is delivered as per study protocol and is critical in the development and testing of evidence-based interventions [40]. Assessing fidelity in the feasibility stage is also critical to identify interventions that have lower than expected fidelity which can then be used to refine interventions prior to a full trial [41]. Fidelity will be monitored by analysing self-reported checklists completed by the treating Physiotherapists. A numerical rating scale (5 point Likert scale) will be used to measure content and quality of the interventions and post-session feedback will be given to the clinicians to improve treatment delivery [42]^.^

**Suitability measures**

Physiotherapists and participants will be asked the appropriateness of outcome measures as well as time and effort required to complete them. Adherence to the intervention will be measured by capturing the number of exercises sessions delivered face-to-face and home exercises remotely monitored by Physitrack app. Qualitative data from the interviews and the focus group will also be collected to develop a training manual and to establish if there is adequate resources and infrastructure at the host hospital to support a definitive trial in the future.

**Acceptability measures**

Acceptability of the interventions will be evaluated during focus groups with participants using qualitative methods.

**Safety**

Safety of the interventions will be determined based on the number and nature of adverse events. All adverse events (related or unrelated to interventions) will be recorded. Components of the prehabilitation interventions are designed not to aggravate patient symptoms. However, in case of worsening of symptoms, the physiotherapist will re-evaluate and adapt the exercises to ensure safety.

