**Table 1. Study objectives and success criteria**

| General objectives | Success criteria |
| --- | --- |
| Recruitment procedure | Participants were recruited within the time constraints of the local NHS hospital |
|  | Participants report that there were no challenges with the recruitment procedure |
| Data collection methods | Data completeness of ≥80% |
|  | Patients and assessors reported that there were no challenges with the data collection methods |
| Follow-up procedures | 100% of participants were contacted for follow-up |
|  | ≥80% completion of follow-up outcome measures |
| Specific objectives | **Success criteria** |
| *Feasibility* | |
| Participant recruitment rates | The recruitment rate of this study will be considered sufficient if at least 33% of eligible patients are recruited over a period of 18 months (n=60). |
| Attrition rate | <30% dropout |
| Usability of Physitrack | Patients and Physiotherapists reported no challenges with the use of Physitrack and telehealth system. |
| Capacity (time and effort) of clinicians to deliver the programme | Physiotherapists report that they had adequate time and resources available to deliver the programme |
| Treatment fidelity | ≥80%  completion of the self-reported checklist |
|  | Physiotherapists reports that there were no barriers identified in the use of self-reported checklists. |
| *Suitability* | |
| Outcome measures | Patients and assessor report that the outcome measures were appropriate and self-explanatory |
|  | Data completeness of  ≥80% |
| Adherence to the programme | ≥70%  of the sessions (face to face + home ex monitored by Physitrack) |
| Time required to undertake each stages of the study | Physiotherapists report that they had enough time to complete each stages of the study. |
| Service infrastructure | Recruitment targets met  Data completeness of ≥80%  Clinicians and researchers report that there was adequate infrastructure to allow completion of a full trial. |
| *Acceptability* | |
| Intervention | Patients and clinicians report that the programme was appropriate and satisfactory |
| Randomisation | Patients are willing to be randomised for a future definitive trial.  (≥80% ) |
| Safety | |
| Intervention | Patients report that the intervention was safe, and no serious adverse events occurred during the prehabilitation phase. |

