**Fig. 2. Timeline for interventions and outcome measures**

**Outcome measures**

- Feasibility outcomes
- iHot-12
- Muscle strength
- SEBT
- HADS
- Pain using BPI
- PGIC

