**8 weeks intervention**

- 1 supervised group education
- 4 supervised in clinic sessions
- Up to 8 remotely supervised sessions using apps & Telehealth

Surgery

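### No adverse-event enquiry common to both arms is stated, so pre-surgery counts by arm would depend on how often participants are seen

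*Protocol*

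**What the plan says.** The Safety section of the protocol gives the measure: "Safety of the interventions will be determined based on the number and nature of adverse events". It adds: "All adverse events (related or unrelated to interventions) will be recorded". It names no recorder, time points, recall period or form of question. The physiotherapist appears there only as the person who reviews and adapts exercises if symptoms worsen.

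Table 1 gives the only safety success criterion: "Patients report that the intervention was safe, and no serious adverse events occurred during the prehabilitation phase".

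For the prehabilitation arm, Fig. 2 lists "1 supervised group education", "4 supervised in clinic sessions" and "Up to 8 remotely supervised sessions using apps & Telehealth" over 8 weeks. The Prehabilitation Intervention section gives a minimum of four clinic sessions and a range of six to eight remote ones. For the control arm, "the usual care intervention consists of advice to continue with normal activities and no prehabilitation therapy".

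Under Trial component, both arms are assessed at baseline, before surgery, and at 6 weeks and 6 months after surgery, with patient-reported outcomes again at 12 months.

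**The concern.** When every event that comes to light is recorded, the total reflects both how many events occur and how many occasions there are to mention one. Before surgery these occasions differ sharply between the arms. A mild flare in a prehabilitation participant can be mentioned within days. The same flare in a usual-care participant has no scheduled outlet until the pre-surgery assessment, by which time it may be forgotten.

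This matters for two reasons. First, unrelated events are counted too, and these can be interpreted only against a background rate. The randomised usual-care arm is the natural source of that rate, and it is the arm likely to be under-counted. Second, the trial is meant to try out data collection for a definitive trial. With no common enquiry, the control-arm half of safety collection would go untested, and no later analysis can recover events that nobody asked about.

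**Working it through.** **Step 1. Scheduled contacts before surgery, prehabilitation arm.**
- Fig. 2: 1 education + 4 clinic + up to 8 remote = 13.
- Supplementary data: Phase 1 is 1 + 2 + 4 = 7 and Phase 2 is 2 + 4 = 6, so 13. This agrees with Fig. 2.
- Prehabilitation Intervention section, minimum: 1 + 4 + 6 = 11. The clinic sessions have no stated maximum there, so 13 is the Fig. 2 figure and not a strict ceiling.

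**Step 2. Scheduled contacts, usual care.** There are none between baseline and the pre-surgery assessment. This is read from the absence of any scheduled contact. A participant could still report an event spontaneously.

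**Step 3. What the imbalance could do to counts.** The documents give neither an event rate nor a recall rate, so everything in this step is assumed:
- the same true risk of 20% over 8 weeks in both arms;
- 30 participants per arm (the upper end of the range in Sample Size);
- events spread evenly over the 8 weeks;
- weekly enquiry with full capture in the prehabilitation arm;
- one enquiry at week 8 in usual care, with recall multiplied by r for each week elapsed.

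Expected events recorded with prehabilitation: 30 × 0.20 = 6.0.

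Fraction captured in usual care: the sum of r^(8−t) for t = 1 to 8, divided by 8. For r below 1 this equals (1 − r^8) / [8(1 − r)].

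| Weekly recall r | Fraction captured | Usual-care events recorded | Apparent ratio |
|---|---|---|---|
| 1.0 | 1.000 | 6.0 | 1.00 |
| 0.9 | 0.712 | 4.3 | 1.40 |
| 0.8 | 0.520 | 3.1 | 1.92 |
| 0.7 | 0.393 | 2.4 | 2.55 |

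For example, at r = 0.7: (1 − 0.0576) / 2.4 = 0.393, and 1 / 0.393 = 2.55. The ratio is 1 divided by the captured fraction, so it does not depend on the assumed 20%. At a 40% risk the counts double and the ratios stay the same.

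**Step 4. Which parts of the safety evaluation are exposed.** Counts of mild events depend on being asked. The Table 1 criterion uses patients' own view of safety and the absence of serious events before surgery. Serious events are far less likely to be missed for want of a contact.

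**The case against.** The strongest reply is that the protocol never undertakes to compare event counts between arms. Its objective is the safety of the intervention, its quantitative analysis is descriptive, and its decision rule in Table 1 needs no comparable counts. This is correct, and it limits the point. A reader might infer that the safety objective cannot be answered, or that the trial will report a false excess of harm. The documents support neither reading.

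A reader might also infer that events are captured only through the treating physiotherapist. The recording sentence is not limited to one arm and names no recorder, so that inference rests on silence. Nor does the protocol say that education or telehealth sessions include an adverse-event enquiry. The 11 to 13 contacts are occasions on which an event could surface, not planned enquiries. Under Interventions, research staff log analgesia for all participants at follow-up, so a route common to both arms exists. It is simply not stated for adverse events.

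The measure list in Fig. 2 does not settle the matter. It includes "Feasibility outcomes", the Feasibility measures section ties feasibility parameters to the Table 1 objectives, and Table 1 includes safety. Adverse events may be meant to fall under that heading. The figure also survives only as fragments of text.

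Finally, the detail may sit in a case report form or an analysis plan that is not shown. A form could supply it. An analysis plan could not, because how and when events are elicited is data collection. What stands is that the protocol makes the number of all events a safety measure and combines it with very unequal contact, without stating a common enquiry.

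**Conclusion.** The point holds in a limited form. Scheduled contact before surgery is 11 to 13 occasions against none between baseline and the pre-surgery assessment, and no enquiry common to both arms is stated. Any description of adverse-event counts by arm would therefore be confounded by contact frequency. The likely direction is towards more recorded events with prehabilitation and too low a background rate in usual care, chiefly for milder events.

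The size is unknown. Under the recall model above, the apparent ratio lies between 1.0 and 2.55 with no true difference, and it vanishes if recall is perfect. Larger false excesses can be produced by choosing harsher capture rates, but nothing in the documents supports a particular value. The Table 1 criterion is much less affected. Safety is also judged on the nature of events as well as their number, which softens the effect further.

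**What to change.** In the Safety section, specify one identical adverse-event question set, covering the period since the last assessment, at the pre-surgery, 6-week, 6-month and 12-month assessments scheduled for both arms. The 12-month questions can go with the patient-reported outcomes by app or post. State that any description of adverse-event counts by arm uses these answers.

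Report events that surface only at prehabilitation sessions separately, and keep them in the intervention arm's own safety evaluation and in the Table 1 criterion. They bear most directly on whether the exercises are safe and must not be lost.

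The cost is a few questions on existing forms and a short addition to the protocol, with no extra visits or staff. The downside is a slightly longer form and some recall error. That error may not be identical in the two arms, because participants are unblinded and those in prehabilitation may already have discussed their symptoms at sessions. The change reduces the ascertainment bias but does not remove it.
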